## Abstract

**Background:**

Traumatic injuries, defined as physical injuries with sudden onset, are a major cause of distress and disability, with far-reaching societal consequences. A significant proportion of trauma survivors report persistent symptoms and difficulties after the injury, and studies show unmet health care needs. Self-management programs delivered in the sub-acute phase after traumatic injuries are scarcely evaluated. The aim of the present study is to evaluate the effectiveness of a self-management program (SEMPO), delivered 3–4 months after moderate-to-severe traumatic injury.

**Methods:**

This study protocol describes a pragmatic randomized controlled trial (RCT) with two classical RCT arms (intervention and control) and an explorative self-selection arm. 220 patients will be recruited from Oslo University Hospital, the largest Trauma Referral Centre in Norway. Patients aged 18–72 years residing in the south-east region of Norway, admitted to the Trauma Centre directly or within 72 h after having sustained a moderate to severe traumatic injury, defined as a New Injury Severity Score > 9, having at least 2 days hospital stay, and reporting injury-related symptoms and impairment at discharge from the acute hospital will be included. Patients will be randomly assigned to either a classical RCT randomization arm (intervention or control arm) or to a self-selection arm. In the randomization arm, participants are further randomized into intervention or control group. Participants allocated to the self-selection arm will choose to partake either in the intervention or control arm. The primary outcome is the level of self-efficacy in trauma coping assessed 6 months after completion of the intervention, with a similar time point for the control group. Secondary outcomes include symptom burden, physical functioning and disability, return to work and health care utilization, health-related quality of life, and communication competency. In addition, patients will be asked to nominate one domain-related measurement as their preferred outcome measure.

**Discussion:**

This RCT will determine the effect of a self-management program tailored to patients with moderate to severe physical trauma, and the self-selection arm incorporates the potential influence of patient treatment preferences on intervention results. If the intervention proves effective, cost-effectiveness and cost-utility analyses will be performed and thereby provide important information for clinicians and policy makers.

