#### Outcome measures

When evaluating the effectiveness of complex interventions, it is recommended to use more than one outcome measure [25]. As the intervention aims to improve patients’ level of self-efficacy, the Trauma Coping Self-efficacy Scale [26] was chosen as the primary outcome with the 6-month follow-up (T4) being the endpoint. Secondary outcomes comprise domains such as symptom burden, physical and cognitive functioning, emotional distress, and return to work. Patients will nominate their target problem areas in their own words [27]. They will also be asked to nominate one self-selected outcome measure based on a presented list of domain-related measurements related to fatigue, sleep, pain, physical functioning, cognition, emotional functioning, and vocation. The rationale for including a patient-preferred outcome measure to ensure participant involvement and patient-centered outcome measurement. Their preferred outcome domain will be established as their self-selected secondary outcome at baseline. Additional outcomes include health-related quality of life, resilience, disability and global functioning, and patient impression of changes. All outcome measures are validated and presented in Table 2. The Trauma Coping Self-Efficacy Scale, the communication with physicians, and the Health Literacy Questionnaire were translated into Norwegian using the established translation procedures by a professional translation service (Forward translation; Expert panel discussion; Back-translation; Final version) [28]. Data for cost-effectiveness and cost-utility will be based on patient-reporting surveys of the type and frequency of received health care services. See Table 2 for an overview of the included outcome measures.

**Table 2 Tab2:** Description of outcome measures utilized in the RCT

Domain:	Outcome measures:	Description:	Time point

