### Sample size

The sample size was estimated based on the primary outcome, the Trauma Coping Self-Efficacy Scale questionnaire [26]. The questionnaire is a 9-item scale answered on a scale ranging from 0 (not capable) to 7 (totally capable). A mean difference in the Trauma Coping Self-Efficacy Scale of 0.6 between baseline and follow-up between the groups is considered as a clinical relevant difference (ref). In order to detect a mean between-group difference of 0.6 with an estimated standard deviation of 1, equal allocation to both groups, 80% power, and a significance level of 5%, we will need to include a minimum of 45 patients in each group and a total of 90 participants [51]. With an assumed attrition rate of 20%, 110 patients will be included (i.e., 55 patients in each group). The sample size calculation was done based on the classical randomization arm (RA), and we aim to achieve the same power in the self-selection (SA) arm. However, the SA is considered an exploratory part of this study to evaluate the influence of patients’ treatment preferences. According to a previous longitudinal study at OUH, approximately 310 patients with trauma-related disability from 18 to 72 years of age may meet the inclusion criteria [52]. Based on previous studies, approximately 70–80% will be eligible for inclusion, resulting in 218–249 eligible patients per year.

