#### Health economics analysis

Cost-effectiveness and cost-utility analyses of SEMPO compared to standard of care will be based on the effectiveness, measured by self-efficacy, symptom burden, global functioning, and quality-adjusted life years (QALYs). Use of healthcare and social support services (categories of service, quantities, and unit costs) collected during the study period, will be used to estimate total costs according to groups. In addition, vocational and educational rehabilitation, equipment and assistive technology, income, and informal care provided by family and significant others will be registered. We will estimate clinical effectiveness in QALYs using standardized conversion tools to convert health benefits into an index of HRQoL, as measured by EQ-5D [40]. Further, simulated cost consequences of the program will be considered from both a healthcare and societal perspectives [55]. Based on the estimated costs and QALYs, we will estimate the incremental cost-effectiveness ratio (ICER), defined as the differences in costs of the SEMPO and standard of care, relative to differences in QALYs of SEMPO and standard of care. Uncertainty will be presented by bootstrapping.

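### The abstract makes the economic evaluation depend on an undefined finding of effectiveness, while the methods plan it without any condition

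*Protocol article*

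**What the plan says.** The Discussion paragraph of the abstract states: "If the intervention proves effective, cost-effectiveness and cost-utility analyses will be performed". Nothing there or elsewhere in the article says which outcome, which follow-up or what criterion would show effectiveness for this purpose.

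The Health economics analysis section carries no such condition: "Cost-effectiveness and cost-utility analyses of SEMPO compared to standard of care will be based on the effectiveness, measured by self-efficacy", followed by symptom burden, global functioning and QALYs. It goes on: "we will estimate the incremental cost-effectiveness ratio (ICER), defined as the differences in costs of the SEMPO and standard of care", set against the difference in QALYs, with uncertainty presented by bootstrapping.

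Objectives lists evidence on relative effectiveness and cost-effectiveness among the hypotheses, again unconditionally. Data collection does not depend on the result either. Outcome measures says "Data for cost-effectiveness and cost-utility will be based on patient-reporting surveys of the type and frequency of received health care services", and Tables 1 and 2 schedule costs, health care utilization and EQ-5D during follow-up.

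**The concern.** One document gives two answers to whether a planned analysis will be done. If the abstract's condition were applied, three things would follow.

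- The decision would be taken after the results are known, under a rule that is not written down. Statistical methods puts several outcomes through mixed models over four time points, so there is more than one way to judge the programme effective.
- A listed aim could go unanswered although the data for it had been collected. Cost-effectiveness depends on costs and effects jointly. Objectives also predicts lower use of health care resources, so an inconclusive self-efficacy result does not settle the economic question.
- The patients whose results satisfy the condition also supply the effect estimate. Running the analysis only after a favourable result selects high estimates of the self-efficacy effect, which is one of the effectiveness measures named for the economic evaluation.

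**Working it through.** **Inputs (Sample size section).** The design assumption reads "In order to detect a mean between-group difference of 0.6 with an estimated standard deviation of 1", with equal allocation, 80% power and a 5% level. The stated size is "we will need to include a minimum of 45 patients in each group and a total of 90 participants". With 20% attrition the plan recruits 55 per group, which leaves 55 × 0.8 = 44.

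**Assumptions made here.** The condition is read as a positive result at two-sided p<0.05 on the primary outcome. The estimate is treated as normal with an unadjusted two-sample standard error. The document states neither.

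**The plan's own figure.** n = 2(1.96 + 0.84)² × 1² / 0.6² gives 44 per group after rounding up. The t-test calculation gives 44.6, so 45, as stated. Power with 45 per group is 0.812 (normal) or 0.804 (t-test). The sample size reproduces.

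**Effect of the condition, 45 per group.**

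- SE = √(2/45) = 0.211, so the smallest significant difference is 1.96 × 0.211 = 0.413.
- For a true difference δ, let a = (0.413 − δ)/SE. The condition is met with probability P = 1 − Φ(a). The mean estimate, given that it is met, is δ + SE × λ, where λ = φ(a)/P.
- For δ = 0.6: a = −0.886, P = 0.812 and λ = 0.332. The mean estimate is 0.6 + 0.211 × 0.332 = 0.67, which is 1.12 times the truth. The analysis is skipped in 1 − 0.812 = 19% of trials.

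| True difference | Condition met | Skipped | Mean estimate if run | Ratio to truth |
|---|---|---|---|---|
| 0.6 (design value) | 0.81 | 19% | 0.67 | 1.12 |
| 0.5 (assumed) | 0.66 | 34% | 0.62 | 1.23 |
| 0.4 (assumed) | 0.47 | 53% | 0.58 | 1.44 |
| 0.3 (assumed) | 0.30 | 70% | 0.55 | 1.82 |

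With 44 per group the results barely move. At 0.6, P = 0.804 (20% skipped) and the ratio is 1.12. At 0.3, P = 0.290 (71% skipped) and the ratio is 1.84.

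**Cost per QALY.** Selection on self-efficacy shifts the mean QALY difference by r × λ standard errors of that difference, where r is the correlation between the two estimates. The document does not give r. For an assumed r of 0.2 to 0.5, the shift is 0.07 to 0.17 SE at δ = 0.6 (λ = 0.332) and 0.23 to 0.58 SE at δ = 0.3 (λ = 1.168). It is zero if r = 0. The cost difference may shift too, and nothing in the document allows that to be sized.

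**The case against.** The strongest reply is that the condition stands in a single abstract sentence about the trial's value to clinicians and policy makers, whereas the methods section is the operative plan. If the methods govern, nothing is skipped and nothing is selected. That is right: every consequence worked out above is contingent on the abstract being followed. It does not remove the conflict, since the document does not say which statement prevails.

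Three stronger readings are tempting, and the document does not support them.

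- *The plan conditions on statistical significance.* A reader might infer this, but the abstract gives no threshold and no outcome. Significance on the primary outcome is the natural reading, yet it remains an assumption. A condition that other outcomes could also satisfy would change the skip rates.
- *The cost-per-QALY ratio is inflated by 12% or more.* The ratios in the table apply to the self-efficacy difference. The ICER is defined on QALYs, and its bias depends on a correlation and on any shift in costs, neither of which is given.
- *A cost-saving programme would never be evaluated.* Health care utilization is itself an outcome in Table 2, and the control-group section says services are logged so that the groups can be compared. Lower resource use would be visible without an ICER. What would be lost is the formal economic evaluation.

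Two further cautions stand. The only effect size in the protocol is 0.6, and the smaller values are illustrations. The planned mixed model may also have a precision different from the simple standard error used here.

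**Conclusion.** The contradiction is real and lies in the current text, and it concerns more than wording, because it bears on whether a planned analysis takes place. If the abstract's condition were applied as two-sided p<0.05 on self-efficacy, with about 45 per group and SD 1, a listed aim would go without its formal analysis in about one trial in five at the design difference. The self-efficacy effect entering the evaluation would be overstated by about 12% on average when it is run. Both figures worsen if the true effect is smaller. The direction and size of any bias in the ICER are not established. The primary effectiveness analysis, the sample size and the data collection are unaffected.

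**What to change.** Delete the condition from the abstract. In Health economics analysis, add one sentence stating that the economic evaluation will be done and reported whatever the effectiveness result, giving incremental costs and incremental QALYs with their joint uncertainty from the bootstrap already planned. The cost is one sentence, plus the work of analysing data that will have been collected anyway if the primary result is null.

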**Trial registration:**

The study is registered in Clinical Trials with the identifier: NCT06305819. Registered on March 05, 2004.

**Supplementary Information:**

The online version contains supplementary material available at 10.1186/s13063-024-08492-0.

## Introduction

### Background and rationale

Traumatic injuries, defined as physical injuries with sudden onset, are a major cause of distress and disability, with far-reaching societal consequences [1]. Traumatic injuries may cause difficulties in physical, cognitive, emotional, and behavioral functioning. A significant proportion report problems in daily life activities, impaired physical and mental health, and reduced quality of life years after the injury [2–4]. This may subsequently limit participation in work, studies, leisure activities, and family life.

Results from a Norwegian multi-center follow-up study on rehabilitation service provision after trauma showed that approximately 50% had a persistent disability at 12 months post-injury, as assessed with the Global Outcome Scale Extended (GOSE) [5]. Patients report prolonged problems with physical, cognitive, and emotional functioning, as well as pain, fatigue, sleep impairment, and reduced participation. Furthermore, preliminary results from the follow-up study demonstrated that 59% and 46% had unmet needs for health care and rehabilitation services 6 and 12 months after the injury. A previously published study on persons with moderate to severe traumatic injury demonstrated that persons who had a pre-injury comorbidity, a higher number of injuries, and higher estimated rehabilitation needs were at risk of poorer functional outcomes 1 year after the injury [5].

Also, persistent disability has emerged as a potential mediating factor for the delayed onset of psychological issues [6, 7]. Despite the fact that most recovery occurs within the first 6 months after injury, the frequency of post-traumatic stress symptoms has shown to remain high [8], and commonly with a delayed onset following traumatic injury [9]. Taken together, interventions aiming to reduce psychological distress in the context of disability should be included in all phases of rehabilitation after traumatic injuries, particularly in the sub-acute phase to support resilient recovery trajectories. Although the need to improve rehabilitation services and provision, including shared decision-making and self-management approaches has been acknowledged [10], rehabilitation following traumatic injuries is still under-prioritized, and self-management approaches are lacking.

The concept of self-management support (SMS) refers to the systematic provision of education and supportive interventions to increase patients’ skills and confidence in managing their health problems, which is in line with the principles of user involvement and patient-centered health services [11]. Self-management as a health concept builds on the theory of self-efficacy developed by Bandura [12] and relates to one’s confidence in the capability to organize and execute the courses of actions required to produce given attainments related to health [11]. Self-management programs aim to enhance self-efficacy by building skills in decision-making, use of available resources, goal setting, and action planning [13]. Self-management also builds on theories of problem-solving, understood as the capacity for effective and adaptive ways of coping with problematic life situations [14].

To date, self-management programs have primarily been directed toward persons with chronic conditions such as asthma, arthritis, diabetes, mental illness, pain, cancer, and AIDS [15]. Studies of self-management interventions have shown significant improvements in health behavior, health status, self-efficacy, fatigue, health-related quality of life, and health care utilization [15–18]. Surprisingly, few studies have investigated the effectiveness of such programs in the early phases of injury or illness, and knowledge concerning the effectiveness of SMS programs for those with traumatic injuries is lacking. Of note, a manualized program developed for chronic disease covers topics that overlap with problem areas reported by the trauma population, such as physical, cognitive, and emotional functioning, fatigue and sleep management; and the use of community resources [15]. One study applied a self-management intervention tailored to the early phase after stroke. The results showed positive changes in self-efficacy, functional activity, social integration, and quality of life [17]. Considering the long-term symptom burden and disabilities following trauma, in addition to the uneven distribution of rehabilitation services, there is a need to investigate the effect of self-management support on patients with persistent injury-related symptoms and difficulties in the sub-acute phase. A recent meta-analytic review by Carlisle et al. found that the choice-based behavioral and mood intervention may enhance participant retention and adherence and may be beneficial to the outcome as well [19]. In order to improve the evidence- base they recommended to consider the provision of choice when designing research and interventions.

It is believed that giving patients the choice to select the treatment or not may improve patient satisfaction and preferences. This may be essential to good clinical practice because the patient’s cooperation and satisfaction reflect the degree to which medical intervention fulfills his or her choices, values, and needs.

### Objectives

The main objective of this study is to determine the effectiveness of a self-management program aiming to support recovery trajectories and prevent chronic problems in patients with moderate to severe traumatic injuries. A self-management support program, SEMPO, was developed for patients in the sub-acute phase of moderate to severe traumatic injury.

The SEMPO is a group-based intervention that includes eight weekly sessions focusing on a specific topic, and it is theoretically based on self-management principles and established rehabilitation strategies. The intervention comprises several ingredients, including psychoeducation, guided skills mastery, learning and practicing helpful compensatory strategies and problem-solving techniques, as well as sharing coping experiences.

We hypothesize that compared to the control group, SEMPO will result in:Increased self-efficacy in managing health problemsImproved health, reduced disability, and use of fewer health care resourcesImprovement in target problem areas and lower burden of trauma-related problemsEvidence on the relative effectiveness and cost-effectiveness of SEMPO compared to standard services

We further anticipate that:Self-selected partaking in the intervention will enhance self-efficacy and level of function of the self-nominated outcome, as well as maximize adherence and reduce potential attrition biasImplementation fidelity will be high and the intervention will be deemed acceptable by participants and therapists

### Trial design

The proposed study is a pragmatic parallel-group randomized controlled trial (RCT) with a mixed method design. The study design includes the classical RCT design with randomization to intervention and control arm. In addition, patients could be randomized to a self-selection arm where they can choose to be allocated to either the intervention or control arm. This is considered as an exploratory part of the study to explore whether the patients’ treatment preferences will maximize adherence, reduce potential attrition bias, and influence the intervention results [20]. Hence, this innovative pragmatic RCT seeks to align the study design to patient-centered treatment, where the influence of patient treatment preferences on intervention effect and adherence will be explored.

Patients who consent to participate will undergo a baseline assessment (T1) before being randomized to either the randomization (RA) arm or self-selection (SA) arm. Follow-up assessments will take place after the completion of the 8-week SEMPO program (T2) and at 3 (T3) and 6 months (T4) after completion of the intervention, with similar follow-up time points for the control group. A feasibility study will be conducted before the full-scale RCT. Additionally, a process evaluation will be performed. This mixed-method design is in line with an updated recommendation by the British Medical Research Council [21].

## Methods: patients, interventions, and outcomes

### Study setting

The study will be conducted at Oslo University Hospital (OUH), Dept. of Physical Medicine and Rehabilitation. OUH is the trauma referral center for the South-eastern region of Norway and has a population base of more than half of the Norwegian population. The feasibility study was conducted from autumn 2023 until January 2024, while the recruitment of patients for the RCT started in January 2024 and will continue until the required sample size has been reached. All baseline assessments will be performed at OUH, interventions either at OUH or by telehealth, while follow-ups will be performed either at OUH or by phone.

### Eligibility criteria

The study population consists of persons aged 18–72 years residing in the southeast region of Norway, who are admitted to OUH directly or within 72 h after having sustained a moderate to severe traumatic injury, defined as a New Injury Severity Score (NISS) > 9 [22], who have at least a 2-day hospital stay, and report injury-related symptoms, functional impairment, and/or difficulties with daily life activities at discharge from the acute hospital stay. Those who consent to participation and are allocated or by self-selection choose to be in the treatment group, will receive SEMPO 3–4 months after the injury.

Exclusion criteria are cognitive functioning corresponding to a Mini-Mental Health Status [23] score < 20 points, severe psychiatric disease or drug/alcohol dependence requiring treatment, complete spinal cord injury or isolated abdominal or thoracic injuries, and insufficient command of Norwegian. The reason for excluding persons with complete spinal cord injuries is that these patients undergo comprehensive long-term rehabilitation of which we will not interfere. The reason for excluding persons with isolated abdominal or thoracic injuries is that a previous Norwegian longitudinal follow-up study demonstrated that these patients seldom have rehabilitation needs [24]. Severe psychiatric disease or drug/alcohol dependence requiring treatment will be excluded due to likely interference with participation and treatment outcomes (Table 1).

**Table 1 Tab1:** Standard Protocol Items: Recommendations for Interventional Trials (SPIRIT)

